### Data collection

Patients will be followed up starting approximately 10 days after treatment and then at 3, 6, 12, 24 and 60 months. A summary of the data to be collected at each visit is shown in table 2. Unscheduled visits may occur at any time during the study in case of a medical emergency or if the investigator deems it necessary for patient care. Unscheduled visits will not be documented.

**Table 2 T2:** Study schedule

Assessment parameters	Visit 1	Visit 2	Visit 3*	Visit 4*	Visit 5*	Visit 6*	Visit 7*	Visit 8*
	Screening/preoperative	Treatment day	Postoperative 10 days (±7 days)	3 months (±30 days)	6 months (±45 days)	12 months (±60 days)	24 months (±90 days)	60 months (±90 days)
Patient information/consent	X†							
Eligibility	X†							
Baseline characteristics	X†							
Reason for refusal of TMJ replacement		X‡						
Treatment details§		X						
Pain medication	X†			X	X	X	X	X
Clinical and functional outcomes	X†		X	X	X	X	X	X
PROs	X†		X	X	X	X	X	X
Anticipated treatment or condition-related AEs	X	X	X	X	X	X	X	X
Survival			X	X	X	X	X	X
Image collection	X†		X			X	X	
Radiographical parameters¶			X			X	X	

* All postoperative FU visits within the defined time windows are calculated from the treatment day (ie, day 0).

† Assessment for patients who will undergo TMJ replacement and for patients who refused TMJ replacement.

‡ Only for patients who refused TMJ replacement.

§ For enrolled patients who underwent total TMJ replacement on one side only and have to undergo TMJ replacement on the contralateral side later during the study, details of additional surgical treatment will be collected at any time during the study.

¶ All images are taken according to local standard-of-care (routine) procedures.

AE, adverse event; FU, follow-up; PRO, patient-reported outcome; TMJ, temporomandibular joint.

#### Baseline information

Demographic data (year of birth, gender and smoking status) will be recorded for each patient. Smoking status includes whether they have a history of habitual smoking, whether they currently smoke and details on the quantity and year of use. Additionally, the use of any tobacco or nicotine products, such as cigarettes, cigars, electronic cigarettes, chewing tobacco, smokeless tobacco, nicotine patches or nicotine gum, will be documented.

Comorbidities will be assessed using the Charlson Comorbidity Index.^33^

#### Diagnosis

The disease/problem to be reported includes trauma, ankylosis, degenerative joint disease, autoimmune/inflammatory joint disease, tumours, osteonecrosis, congenital deformity, infectious diseases and others.

Signs and symptoms to be reported include the year of onset of TMJ-related problems, the affected side and the following current signs and symptoms:

Fracture/condylar damage.Restricted mouth opening.Occlusal derangement.Condylar resorption/loss of height of the vertical ramus.Jaw movement restrictions.Crepitus, clicking and other joint noises.Failed previous implant.Pain.Difficulties in eating.Airway obstruction.Joint dislocation/subluxation.Other.

Previous and current treatments will be recorded, including the type of conservative treatment used (both previous and current) and the number, type and year of any prior surgical treatments. The year and reason for refusal of alloplastic total TMJ replacement will also be recorded, along with current and previous pain management treatments and oncological treatment (in cases of tumour).

For patients who refused alloplastic total TMJ replacement surgery, the reasons for refusal will be documented.

#### Treatment details

Surgical details to be documented include:

Side (left, right or bilateral).Date and duration of the surgery (minutes).Use of preoperative virtual surgical planning.Implant type (stock or customised implants, brand).Material (mandibular and fossa components).Screws used (normal or back-up/safety), including side (left/right), number, length and diameter.Details of surgical approach as per AO standards (preauricular, retromandibular, submandibular or facelift).^34^Use of intermaxillary fixation (intraoperative or postoperative).Length of hospitalisation (days).Details of antibiotics and steroids.Details of functional rehabilitation (type and duration).Details of the type and frequency of pain medication (if indicated).

If applicable, additional surgical procedures (eg, dental extractions, orthognathic surgery, coronoidectomy, eminectomy, resection, reconstruction, bone or fat grafting, soft tissue flap, hardware removal) will be recorded. If a contralateral TMJ replacement is performed during the study, surgery details will be collected.

#### Premature termination of participation

Participants may be terminated early for reasons including withdrawal of consent, the investigator’s discretion (eg, non-compliance), the sponsor’s decision, loss to follow-up (FU), failure to undergo TMJ replacement (excluding those who refused surgery), death, ineligibility or other reasons. Detailed information explaining the circumstances leading to premature termination will be documented in a dropout form. For these participants, data collected up to the termination date will be censored. Censored data will be included in the analyses.

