#### Survival

Patient’s survival will be documented at each FU visit. If a visit is missed, survival will be confirmed by phone call.

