### Statistical analysis

Since the objectives of this registry are descriptive and exploratory in nature, no formal hypothesis testing is planned, and all analyses will be exploratory. The planned sample size of 200 patients is based on the estimated number of eligible participants expected to be enrolled during the 2-year recruitment period. Eligible patients who refuse TMJ replacement will be included in the study but excluded from sample size calculations. Depending on the volume and quality of the data collected during the first 2 years, the registry may remain open thereafter, with patient FU of up to 5 years.

A detailed statistical analysis plan (SAP) will be finalised before the final analysis (ie, the analysis from which the results will be summarised in the final registry report). As the primary aim of the current registry is descriptive, patient characteristics, clinical data and outcomes recorded at standard-of-care scheduled FU assessments will be presented using descriptive summary statistics. Categorical variables will be summarised using frequency and percentage for each category. Continuous variables will be summarised using the mean, SD, median, IQR and minimum and maximum values. Analyses will also be stratified by clinically relevant categories, including treatment patterns.

Longitudinal clinical, functional and PRO data may be analysed using mixed-effects models for repeated measures, allowing inclusion of all available data and minimising the impact of missing data. Time-to-event analyses are planned, with survival status recorded at each scheduled FU. Kaplan-Meier methods will estimate survival probabilities, and multivariable Cox proportional hazards models will be used where event numbers permit.

Centre effects and geographic variability will be addressed using multilevel (hierarchical) models with patients nested within regions to account for clustering and differences in practice patterns. For time-to-event outcomes, region (or treating centre) will additionally be included as a covariate in Cox regression models when sample sizes permit. The AEs will be summarised at both patient and event levels, with rates calculated using the total population as the denominator, regardless of dropouts, with 95% CIs provided.

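### The termination rule, read literally, censors deaths, although death is the event in the planned patient-survival analysis

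*Protocol article*

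**What the plan says.** Under Premature termination of participation, the protocol article lists reasons for ending participation early. Withdrawal of consent and loss to follow-up are among them, and the list closes with "failure to undergo TMJ replacement (excluding those who refused surgery), death, ineligibility or other reasons". Two sentences then govern the data of all these participants: "For these participants, data collected up to the termination date will be censored", followed by "Censored data will be included in the analyses". Neither sentence sets death apart.

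The Survival section concerns the patient's vital status, not the implant: "survival will be documented at each FU visit". It adds: "If a visit is missed, survival will be confirmed by phone call". Table 2 carries a Survival row at every postoperative visit, from 10 days to 60 months.

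The Statistical analysis section says: "Time-to-event analyses are planned, with survival status recorded at each scheduled FU". It continues: "Kaplan-Meier methods will estimate survival probabilities, and multivariable Cox proportional hazards models will be used where event numbers permit". It names no other event for these analyses.

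**The concern.** A censoring rule must separate the event of interest from the other ways in which observation ends. Here one rule covers withdrawal, loss to follow-up and death alike, while patient survival is the only outcome named for the Kaplan-Meier and Cox methods. An analyst or programmer who follows the termination section would code each death as censored and so remove every event from the analysis.

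The sentence has a second fault. Data collected up to termination have been observed and are not censored. What is censored is the unobserved time afterwards. As worded, the rule does not say correctly what happens to either part.

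At stake is the patient-survival estimate over up to five years, and any Cox model built on it.

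**Working it through.** The article states no survival probability, mortality or expected number of deaths, so there is no figure of its own to reproduce. The check is what the stated rule does to the stated estimator.

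**Inputs from the article**
- Death is a premature termination, and data of terminated participants are censored (Premature termination of participation).
- The outcome is patient survival, estimated by Kaplan-Meier, with Cox models where event numbers permit (Survival; Statistical analysis).
- Planned size is 200 and follow-up runs to 60 months (Statistical analysis; Data collection). The 200 is a feasibility number and is used here only for illustration.

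**Step 1: the estimator under the literal rule**

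S(t) = product over event times t_i ≤ t of (1 − d_i / n_i), where d_i is the number of deaths counted as events at t_i and n_i is the number at risk.

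If every death is coded as censored, every d_i = 0 and every factor is 1. So S(t) = 1 at all t. A Cox partial likelihood has one term per event, so with no events there is nothing to fit. This step needs no assumption about mortality.

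**Step 2: how many deaths would vanish**

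The mortality rate r per year is an assumption. Expected deaths in 200 patients over 5 years without dropout = 200 × (1 − exp(−5r)).

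| Assumed r per year | Expected deaths | True 5-year survival, exp(−5r) | Estimate under the literal rule |
|---|---|---|---|
| 0.2% | 2.0 | 99.0% | 100% |
| 0.5% | 4.9 | 97.5% | 100% |
| 1.0% | 9.8 | 95.1% | 100% |

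**Step 3: simulation check**

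200 patients, 60 months, exponential death times, 1,000 runs per scenario. The 5-year mortality and dropout are assumptions.

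| 5-year mortality | Dropout | Mean deaths | Mean S(60), death as event | Mean S(60), literal rule |
|---|---|---|---|---|
| 2% | 0% | 4.0 | 0.980 | 1.000 |
| 2% | 20% | 3.7 | 0.980 | 1.000 |
| 5% | 0% | 9.9 | 0.950 | 1.000 |
| 5% | 20% | 9.1 | 0.949 | 1.000 |
| 10% | 0% | 20.1 | 0.900 | 1.000 |
| 10% | 20% | 17.9 | 0.900 | 1.000 |

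With death as the event and other exits censored, the estimator recovers the assumed survival. Under the literal rule it never moves from 1.

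**Step 4: does the next sentence rescue the rule?**

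The sentence that censored data will be included keeps these patients in the risk set up to termination. It does not turn a death into an event. If both sentences mean only that collected data are kept, the 100% result no longer follows. The article then has no statement of how death is classed in the survival analysis, and its censoring sentence still says something else.

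**The case against.** The strongest reply is that this is a loose sentence in a section on participation, not an analysis specification. It may mean only that data gathered before dropout are kept, and the sentence after it supports that. The more specific sections also suggest that deaths are meant to count: survival is recorded at every visit, a phone call confirms it when a visit is missed, and a condition on event numbers presupposes events. A detailed SAP is promised, and event and censoring definitions commonly sit there. Patient survival is not named in the Objectives, all analyses are exploratory, and a handful of deaths would hardly support a multivariable Cox model with 12 listed covariates.

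Much of this stands. It makes the intent fairly clear and limits the consequence. It does not remove the conflict: the article does not leave the matter to the SAP but states a rule, includes death in it, and plans an analysis that the rule defeats. An SAP that counts death as the event would depart from the published text.

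Three further readings may tempt a reader, and the article does not support them:
- **Non-compliance contradicts the phone call.** The phone call concerns a missed visit. Ending participation at the investigator's discretion is a different matter, and nothing says that a missed visit leads to it. Whether to keep that reason is a preference about participation rules, not an error.
- **Revision is also followed by phone.** The call confirms survival only. Revision surgery is listed as an adverse event, and adverse events are summarised as rates.
- **Death is mishandled as a competing event.** No time-to-event outcome other than survival is named, so the point is hypothetical.

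**Conclusion.** The concern holds as a conflict within the stated rule. Followed literally, the termination section censors every death and fixes estimated patient survival at 100%. That result is algebraic and rests on no assumed mortality; only the number of deaths lost does (about 2 to 10 in 200 patients at 0.2% to 1.0% per year). The sentence is also wrong in labelling as censored the data observed before termination.

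A reader might infer that the registry will in fact report 100% survival. The article does not support that: its survival follow-up points to deaths being captured and counted, and the SAP is not shown. The text should be corrected because a stated rule gives a wrong result if applied, and the correction is cheap.

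**What to change.** Replace the censoring sentence under Premature termination of participation with wording such as:

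> Data observed up to termination are retained in all analyses. In the survival analysis death is an event at its date; all other terminations are right-censored at the last date the patient was known to be alive.

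Make sure that the existing dropout form and the survival entry at each visit record the date of death and the last date known alive, and carry the same definition into the SAP. The cost is two sentences and, if not already captured, two date fields. No change to sample size, visits or participation rules is needed.

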### Outcome measures

Clinical and functional outcomes, PROs and radiological parameters will be collected according to the schedule outlined in table 2.

#### Clinical and functional outcomes

Clinical and functional outcomes to be assessed include:

Mandibular movements: measurement of interincisal/maximal opening, lateral movements and protrusive movements.^35^ Each movement is scored, and the total score is used to determine a mobility index, which distinguishes between normal mandibular mobility (0 points), slightly impaired mobility (1–4 points) and severely impaired mobility (5–20 points).Occlusal status: assessed according to Angle’s classification.^36^Dental status: recorded as edentulous, complete or partial dentition; missing teeth recorded using the Fédération Dentaire Internationale tooth numbering system.Mandible dysfunction: evaluated by means of the Helkimo Index (clinical dysfunction [D_i_] component),^37^ which assesses five different symptoms (impaired range of movement, impaired TMJ function, muscle pain, TMJ pain and pain on movement of the mandible). Each symptom is scored as 0 (normal), 1 (mild) or 5 (severe), giving a total score of 0–25. Patients are classified according to severity as follows:D_i_ 0, clinically symptom-free (0 points).D_i_ I, mild dysfunction (1–4 points).D_i_ II, moderate dysfunction (5–9 points).D_i_ III, severe dysfunction (10–13 points).D_i_ III, severe dysfunction (15–17 points).D_i_ III, severe dysfunction (20–25 points).

#### Patient-reported outcomes (PROs)

The PROs assessed in this study include the pain numeric rating scale (NRS), the jaw function NRS, the diet limitation NRS, the EuroQoL five-dimension five level (EQ-5D-5L) questionnaire and the oral health impact profile-14 (OHIP-14).

The *pain NRS* measures pain intensity on an 11-point scale from 0 (no pain) to 10 (worst pain imaginable), reflecting overall or average daily pain.

The *jaw function NRS* is also an 11-point scale from 0 (normal jaw movement) to 10 (no jaw movement), assessing subjective jaw function.

The *diet limitation NRS* evaluates diet limitation on an 11-point scale from 0 (no restrictions) to 10 (liquids only).

The *EQ-5D-5L* is a standardised instrument for assessing health-related QoL and provides a generic measure that enables comparisons across different health conditions as well as health-economic analyses. It includes five dimensions: mobility, self-care, usual activities, pain/discomfort and anxiety/depression. Each dimension has five levels of severity, ranging from no problems (level 1) to extreme problems (level 5). The level chosen by the respondent for each dimension creates a 5-digit health profile.^38^ Validated translations are available in the local languages of all participating study sites.

The *OHIP-14* was chosen to capture oral health-specific impacts that are particularly relevant to TMJ pathology and its functional consequences. The instrument measures oral health-related QoL by focusing on impairment across three functional status dimensions—social, psychological and physical—which correspond to four of the seven QoL dimensions proposed by Patrick and Bergner.^39^ All impacts measured by the OHIP are conceptualised as adverse outcomes; therefore, the instrument does not assess any positive aspects of oral health. It covers seven domains: functional limitation, physical pain, psychological discomfort, physical, psychological and social disability and handicap. Each domain includes two items, evaluated using a 5-point Likert scale from ‘never’ to ‘very often’, with higher scores indicating worse outcomes.^40^ Validated translations of the OHIP-14 are available in the local languages of all participating study sites.^41^

#### Adverse events (AEs)

Since this is an observational registry, only anticipated condition-related, treatment-related or implant-related AEs will be documented from the time of consent onwards. These include fixation failure (implant loosening, breakage or instability), dehiscence of incision, wound infections, neurological-related (facial nerve damage, Frey’s syndrome, sensory disturbances or altered hearing), bleeding, haematoma, swelling, injury to adjacent structures, ankylosis, malocclusion, sensitivity to material, heterotopic ossification, disarticulation, contralateral joint dysfunction, condylar resorption, graft loss, revision surgery and any other AEs that may affect the outcome of the registry.

These events are considered events of scientific interest, that is, events that can clearly be connected to the treatment(s) or the medical condition under investigation and will not require immediate reporting to the local EC/IRB unless they occur at a higher frequency and/or severity than that cited in the literature.

This registry can be considered a minimal-risk study, given that participation poses a very low risk compared with the standard-of-care (routine) procedures.

#### Survival

Patient’s survival will be documented at each FU visit. If a visit is missed, survival will be confirmed by phone call.

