**Trial registration number:**

NCT03991728.

STRENGTHS AND LIMITATIONS OF THIS STUDYThis is the first prospective, multicentre international registry for total alloplastic temporomandibular joint (TMJ) replacement with up to 5 years of follow-up (FU).The registry will collect high-quality, prospective data on treatment and outcomes from a large cohort of patients undergoing alloplastic total TMJ replacement, providing broader insights into the underlying disease, treatments and outcomes.A limitation of the study is its observational study design, which precludes direct comparison of treatment outcomes across interventions.The extended FU period (60 months) may result in missing data over time.Differences in treatment protocols and reporting standards across participating centres may affect the consistency, quality and comparability of the collected data.

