### Objectives

The study seeks to broaden understanding of TMDs, treatment patterns and patient outcomes, with a focus on clinical indications, regional variations and patient-reported, clinical and functional outcomes in patients undergoing alloplastic TMJ replacement. Additionally, the study aims to identify predictive factors for favourable outcomes (such as pain reduction, range of motion, occlusal status and QoL) and understand why some patients refuse TMJ replacement.

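### The missed-visit phone call is specified for survival alone, so self-reported outcomes and late complications in non-attenders go uncollected, and the AE denominator then counts them as event-free

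*Protocol article*

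**What the plan says.** **Schedule.** The Data collection section states: "Patients will be followed up starting approximately 10 days after treatment and then at 3, 6, 12, 24 and 60 months". Table 2 has no visit between months 24 and 60, and none after month 60.

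**What is tied to visits.** Under Outcome measures: "Clinical and functional outcomes, PROs and radiological parameters will be collected according to the schedule outlined in table 2". Table 2 also schedules AEs at every visit, and pain medication at screening and from month 3 on. Of contacts outside the schedule, Data collection says: "Unscheduled visits will not be documented".

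**Missed visits.** The Survival subsection says: "If a visit is missed, survival will be confirmed by phone call". No other item is named for the call, and no telephone, postal or electronic route for PROs or complications appears elsewhere.

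**Missing data.** The strengths and limitations list concedes: "The extended FU period (60 months) may result in missing data over time". The Statistical analysis section answers with optional mixed-effects models, described as "allowing inclusion of all available data and minimising the impact of missing data". Detailed missing-data rules are left to the SAP.

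**AE rates.** The same section calculates AE rates over the whole population, dropouts included, with 95% CIs.

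**The concern.** The article expects missed visits and already has sites telephoning those patients, but the one item it protects by that call is vital status. The Objectives name pain reduction, range of motion, occlusal status and QoL as the favourable outcomes of interest, and the AE section lists revision surgery and fixation failure. Several of these can be answered by telephone: three single-item 0–10 scales, a five-question EQ-5D-5L, current pain medication, and whether and when a revision or other listed event happened.

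Attendance over five years may well depend on outcome. Patients who do well may stop coming, and patients with problems may go elsewhere. Long-term PRO summaries would then describe attenders. A mixed model corrects this only as far as the missingness is explained by observed values, and it cannot supply a revision that nobody recorded. For AEs there is a second step: with the full population as denominator, a patient whose later history is unknown enters the rate as a patient without the event.

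**Working it through.** The article has no attrition rate, revision rate or power calculation, so there is no stated figure to reproduce. The 200 is a feasibility number. Everything else below is assumed.

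**Inputs**
- N = 200 operated (Statistical analysis)
- m = share missing month 60: assumed 30%, range 10–40%
- Cumulative revision: assumed 10% in attenders and 20% in non-attenders
- c = share of non-attenders' revisions that are captured: assumed 0 at first, then varied

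**AE rate at m = 30%**
- Attenders: 0.70 × 200 = 140, with 0.10 × 140 = 14 revisions
- Non-attenders: 0.30 × 200 = 60, with 0.20 × 60 = 12 revisions
- True rate: (14 + 12)/200 = 13.0%
- Reported under the plan's denominator, c = 0: 14/200 = 7.0% (Wilson 95% CI 4.2% to 11.4%, wholly below 13.0%)
- Half the non-attenders reached and asked: (14 + 6)/200 = 10.0%
- The same data over the 170 patients with AE information: 20/170 = 11.8%

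**Range over m, with c = 0**

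| m | Attenders | Revisions seen | Reported over 200 | True, non-attenders 20% | True, non-attenders 10% |
|---|---|---|---|---|---|
| 10% | 180 | 18 | 9% | 11% | 10% |
| 20% | 160 | 16 | 8% | 12% | 10% |
| 30% | 140 | 14 | 7% | 13% | 10% |
| 40% | 120 | 12 | 6% | 14% | 10% |

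The last column shows that the rate is too low even when non-attenders fare no worse. The denominator alone does that.

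**Sensitivity to c, at m = 30%.** Reported = (14 + 12c)/200: 7.0% at c = 0, 10.0% at c = 0.5, 13.0% at c = 1. Revisions that happened before a patient's last attended visit would normally be on record, so c = 0 is the extreme case.

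**PROs at month 60**
- CI widening relative to full attendance is 1/√(1 − m): 1.05, 1.12, 1.20 and 1.29 for m = 10, 20, 30 and 40%.
- If non-attenders are d = 1 to 2 NRS points worse, the attenders' raw mean pain is too low by m × d: 0.1–0.2 points at 10% missing and 0.4–0.8 at 40%.
- Reaching half the non-attenders at m = 30% raises the number with data from 140 to 170. The CI width ratio is √(140/170) = 0.907, about 9% narrower.

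**The case against.** **The article never says only.** The sentence sits in a short subsection on how survival is ascertained, in an article that condenses a fuller protocol. A reader might infer that other questions are barred from the call; the text does not say so. What stands is narrower: the article does give a missed-visit procedure, survival is the one item in it, and the other outcomes are placed on visits.

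**Complications are not all lost.** A reader might infer that any missed visit loses the complications before it. The AE section says "AEs will be documented from the time of consent onwards", so an event before a missed interim visit can be entered at a later attended one, and a dropout form records why a patient left. This objection holds. The exposed events are those after the last attended visit, chiefly between months 24 and 60 and in permanent non-attenders.

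**A call cannot recover examined outcomes.** Mandibular movement, the Helkimo Index, occlusion and imaging need attendance. Two of the four outcomes named in the Objectives, range of motion and occlusal status, are therefore outside the remedy. Nor do the Objectives name a 60-month timepoint; earlier visits inform them too.

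**Survival has its own use.** Kaplan-Meier analysis is planned with survival status recorded at each follow-up, so the call serves a planned analysis. That is a reason to keep the survival item, not a reason to ask nothing else.

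**Exploratory aims, central checks and a later SAP.** No hypothesis is tested, eCRF completeness is monitored centrally, and missing-data rules go to the SAP. Monitoring shows a gap without giving a way to fill it, and an analysis plan cannot restore answers that were never requested. The article also warns that five PROs may burden patients, which argues for a short set by telephone.

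**Conclusion.** The point holds as a cheap and worthwhile improvement to data collection; it is not a contradiction in the plan. As the article stands, self-reported outcomes at any missed visit, and complications or revisions after the last attended visit, have no stated collection route, and the AE denominator turns the missing events into non-events.

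Under the 30% scenario the reported revision rate is 7.0% against a true 13.0%, a shortfall of 6 percentage points. It ranges from 2 points at 10% missing (9% against 11%) to 8 points at 40% (6% against 14%). These figures rest on assumed attrition, assumed revision rates and no capture among non-attenders. Partial capture shrinks the gap in proportion. The direction rests only on some events being missed while the full population stays in the denominator. If the full protocol already puts these items in the call, one clarifying sentence settles the collection part, and the denominator question remains for any patient who is not reached.

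**What to change.** 1. **Survival subsection and table 2:** state that the call after a missed visit also collects the pain, jaw function and diet NRS, EQ-5D-5L and current pain medication, and the occurrence and date of revision, implant removal and listed AEs since the last contact.
2. **eCRF:** flag each record as telephone or clinic, and use the flag in a sensitivity analysis of the PROs.
3. **Statistical analysis:** do not treat patients without AE follow-up as event-free. For example, censor each patient at the last contact at which AEs were asked about, and report how many patients have AE information through month 60. Step 1 alone is not enough: with half the non-attenders reached, the full-population denominator still gives 10.0% against 13.0%.

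The cost is a few minutes per call, one short eCRF form, and a possible mode difference between telephone and clinic scores, which the flag lets the analysis examine. OHIP-14 is left out of this list to keep the call short, so oral-health QoL stays missing at those visits. Patients who cannot be reached stay missing, and censoring them still assumes that their later event risk resembles that of patients who remain under follow-up.
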